## Abstract

This manuscript describes the rationale and protocol of a school-based randomized controlled trial called “Cycling and Walk to School” (PACO, by its Spanish acronym) that aims to promote cycling to and from school and physical activity (PA) in adolescents. This study will examine the effects of this intervention in cycling and active commuting to and from school (ACS), PA and several ACS-related factors based on self-determination theory (SDT) and a social-ecological model (SEM). A total of 360 adolescents attending six high schools (three experimental and three control) from three Spanish cities will participate in this randomized controlled trial. The intervention (four cycling sessions; 1–2 h per session, one session per week) will be conducted by the research staff; the control group will continue their usual activities. PA levels will be measured by accelerometers, whereas ACS and the other study variables will be self-reported using questionnaires at baseline and post-intervention. The primary outcomes will be: rates of cycling to school, ACS and PA levels. In addition, SDT-related variables and individual, interpersonal, community, and environment variables relevant to ACS will be based on SEM. The findings will provide a comprehensive understanding of the short-term effects of this school-based intervention on cycling to school behaviour, ACS and PA levels in Spanish adolescents.

## 1. Introduction

### 1.1. Active Commuting to School: Benefits, Prevalence and School-Based Interventions

The physical, psychological, and social benefits of meeting physical activity (PA) recommendations (i.e., 60 min of daily moderate-to-vigorous PA [MVPA]) have been well-documented in the scientific literature [1]. However, four out of five adolescents do not meet these MVPA guidelines [2]. Specifically, in Spain, 76.6% of adolescents between 11 to 17 years old are insufficiently active [2]. Since previous studies have shown that PA patterns in childhood track to adulthood [3], promoting regular PA levels in young people is a public health concern [4].

Active commuting to and from school (ACS) is defined as any walking or cycling to and from school; while passive commuting refers to the use of motorized vehicles as a mode of commuting, such as by car, bus, metro, train, or motorcycle, among others [5]. ACS in adolescents is a routine behaviour that is associated with higher levels of PA on schooldays [6,7,8], less time spent in sedentary pursuits [9] and has social and mental benefits [10]. Compared to walking, cycling to school leads to significantly higher physiological benefits, particularly regarding cardiorespiratory fitness, due to its higher PA intensity [6]. In addition, ACS also has environment and economic benefits [11]. Moreover, getting young people physically active during their trip between home and school is currently one of the main priorities of global policies, such as the Global Action Plan on Physical Activity 2018–2030, promoted by the World Health Organization [12], and the 2030 Agenda for Sustainable Development, promoted by the United Nations [13].

However, despite the well-known benefits associated with ACS, fewer than half of adolescents globally use ACS [14], with large variability across countries [9]. In Spain, about 50% of adolescents reported walking to school and only 0.3% reported cycling to school [15]. Although 68.2% of Spanish adolescents and young people aged 12 to 24 years already own a bicycle and 92.2% of them could ride a bicycle [16], less than 2% reported cycling to school [15,17,18,19]. Given that cycling to school tends to track from childhood to adolescence [20], along with its documented benefits, promoting this health-related behaviour should be a public health priority.

Schools have been identified as an ideal setting to promote health-related behaviours such as ACS [21]. However, previous systematic reviews about school-based ACS interventions found non-significant results or small effect sizes [22,23,24,25]. These studies did not differentiate the effects on both walking and cycling to school because active commuting modes were pooled. Future school-based interventions should focus on improving walking or cycling to school separately because these two active modes of commuting have been associated with different health benefits, correlates, and require different skills and equipment [26,27]. However, most ACS interventions to date focused on walking to school (25 studies among 37), whereas studies that examined cycling interventions largely focused on primary school children (7 studies among 12) [22,25]. Therefore, there is a need to evaluate the effects of cycling interventions in secondary schools [23], particularly since the correlates of cycling to school between children and adolescents may also differ [28]. A recent scoping review [29] conducted on cycle skill training interventions reported than three of these six identified studies increased the cycling rates to school [28,30] and most of them reported an increase in student’s general cycling confidence, knowledge, skills, and attitudes [29]. School-based studies to promote ACS conducted to date have had several limitations including lack of use of theories of behaviour change, weak methodological design, and lack of reliable and valid assessment [22,23,24,25,29]. Given that most of the previous school-based cycling interventions have not been based on behaviour change theory, and/or have not used comprehensive and rigorous frameworks to assist with design, implementation, and evaluation of the interventions, further cycle skills training interventions are required to examine whether well-designed interventions can be effective in improving cycling to school [31].

### 1.2. Behaviour Change and Implementation Frameworks: Social-Ecological Model, Self-Determination Theory, and Reach Effectiveness Adoption Implementation Maintenance (RE-AIM) Framework

Findings from promising school-based ACS interventions suggest that the integration of behaviour change frameworks, such as the social-ecological model (SEM) [32] and self-determination theory (SDT) [33], in the design, implementation, and evaluation of these interventions may enhance initiation and long-term maintenance of ACS behaviours [34,35,36,37,38]. The SEM considers that ACS is influenced by different factors: individual (e.g., sex, age, ethnicity, etc.), interpersonal (e.g., family and significant other support), community (e.g., social capital), built environment (e.g., distance, safety, walkability, etc.), and policy (e.g., school policies) [35,36,39,40]. Complementary to the SEM, SDT posits that interpersonal and individual factors can influence the motivational process for ACS [41]. According to SDT, a student’s perception of social support for ACS from others (e.g., parents, teachers, peers, etc.) may have an influence on the student’s basic psychological need satisfaction (i.e., autonomy, competence, and relatedness satisfaction in ACS) which, in turn, may influence autonomous motivation and health-related behaviours such as ACS. The integration of both frameworks provides a better understanding of the motivational processes to actively commute to school [41].

Considering both internal and external validity when evaluating the potential for public health impact of behaviour change interventions remains a priority [42]. The Reach Effectiveness Adoption Implementation Maintenance (RE-AIM) framework has been widely used for this purpose [42,43]. The RE-AIM framework includes reach (R), effectiveness (E), adoption (A), implementation (I), and maintenance (M) [42]. Effective PA interventions have too often been conducted only in controlled settings and more efforts are required to implement and evaluate interventions in real-world contexts [44]. Although the number of school-based PA interventions that have used the RE-AIM framework for evaluation purposes have increased in recent years [45], to the best of our knowledge, no school-based interventions have used this framework to promote ACS. Evaluating all five components of the RE-AIM framework may improve the translatability, scalability, feasibility, and sustainability of interventions to promote cycling to school.

### 1.3. The Pedalea y Anda al COle (PACO) Study Framework

The “Pedalea y Anda al COle: PACO” [Cycling and Walk to School] study has been designed to respond to the main needs, challenges, and limitations of ACS interventions identified in the literature to date [22,23,24,25,29,31,46]. Currently, there are a limited number of ACS interventions focused on promoting adolescent´s cycling to school. Behaviour change frameworks such as the SDT and SEM have been used as theoretical frameworks to guide the design of the PACO study cycling intervention. Finally, the RE-AIM framework will be used to evaluate aspects related to the internal and external validity of this school-based ACS intervention.

The most successful and effective PA interventions in real-world settings are those that have utilized a theoretical framework, identifying the intervention effects on potential mediators [47]. Grounded in SDT and SEM frameworks, as well as the existing evidence about potential mediators of PA [48,49,50], several mediators have been identified in the PACO study to determine which components of an intervention contribute to behaviour change.

The PACO study is a randomized controlled trial study with three main aims developed according to a logic model that identifies mediators and outcomes (see Figure 1).

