### 3.2. Description of the Intervention in the PACO Study

The PACO study comprises a school-based cycling intervention that will aim to promote cycling to and from school and to increase PA levels, while addressing relevant factors within the PE curriculum for secondary education. It is based on the intervention strategies proposed by the Active Living by Design Community Action Model framework [52] including: *preparation* through developing an intentional intervention, *promotion* through educating and encouraging participants on adopting cycling behaviours, and *programs* through organizing activities to engage the participants. These three strategies have been the most commonly used in published ACS interventions [22,25].

The research staff designed the intervention based on previous experience with other school-based ACS interventions and evidence on effective school-based strategies to promote ACS [22,25] and, particularly, cycling to school [53,54]. A main priority was to design a feasible school-based intervention to be implemented within the PE sessions. The intervention objectives, content, components (i.e., knowledge, skills, and attitudes), and the methodological approach are based on the current Spanish national educational law for compulsory secondary education [55]. The contents of the four intervention sessions have been published [56] and are available online (http://profith.ugr.es/pages/investigacion/recursos/manualbici/) to be used by any teacher. Consistent with the RE-AIM framework [42], if the intervention proves effective, it might contribute to promote the adoption and further scale up of this intervention.

The PACO study intervention is based in the Bikeability methodology [57], as a cycle training intervention to gain practical skills and understand how to cycle on roads. Given that the intervention objective is to promote cycling to school, the intervention components and contents are focused on: (a) *knowledge* about road safety rules, cycling safety equipment, cycling hand signals, and the benefits of cycling as a mode of commuting; (b) *skills* related to cycling in a traffic-free and on-road in urban context, and (c) *attitudes* related to awareness, confidence, enjoyment, and usefulness of cycling.

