The 7 h intervention has four sessions that will be implemented during PE sessions over a period of one month (1 weekly session). An expert teacher in cycling in an urban context will lead all the intervention sessions, and the PE teachers will attend to learn and support the sessions. The sessions are described below (see Figure 4):

(1) Theoretical session (60 min—first week): theoretical session in the classroom to provide the participants a first step in the concept of cycling as a mode of commuting in the city. The content will include: awareness about the benefits and usefulness of cycling as a mode of commuting, knowledge about road safety rules for cycling, knowledge about cycling safety equipment for both the rider and the bicycle, and cycling hand signals in urban context.

(2) Closed circuit session (120 min—second week): practical session on the school grounds to learn or improve the fundamental cycling skills needed to ride the bicycle safely. The participants will practice how to fit the helmet and check the bicycle before cycling, as well as the fundamental cycling skills through 10 activities and a cycling circuit. The contents will include: correct helmet fitting, bicycle safety check before the ride, and the fundamental cycling skills of starting off and pedalling, breaking safely, changing gears, and hand signals to change directions.

(3) Urban circuit session (120 min—third week): practical session in urban context on-road traffic to transfer the previously learnt cycling knowledge and skills. The participants will learn advanced cycling skills on-road and will use the previously learnt cycling skills in new, uncertain, and modifiable on-road situations exposed to urban traffic. The content will include: starting from side of road (curb), stopping on side of road (kerb), overtaking a parked or slower-moving vehicle, lane changing, turning right and left, and crossing a roundabout.

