### 4.1. PACO Study Assessment Protocol

In the PACO study, assessments will be performed at baseline (before the 4-week intervention period) and immediately after the intervention period for both intervention and control groups (see Figure 5). A further detailed description has been published [58]. All measurements will be completed at participant’s school by trained research staff during 3 assessment sessions conducted over 9 days both at baseline and after the intervention period:Assessment session 1 (1 h): this session will include anthropometry assessment at an indoor sport facility. During this session, participants will receive their accelerometer and the activity diary as well as a family questionnaire for their parents to complete at home.Assessment session 2 (1 h): participants will receive their GPS unit and corresponding instructions.Assessment session 3 (1 h): during this classroom-based session, participants will return their accelerometer, the activity diary, the GPS unit, and the completed family questionnaire. During this session, participants will also complete a student questionnaire online or on paper. The questionnaires will be subsequently read using DataScan [59] to guarantee an objective process.

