## 6. Data Analysis

Descriptive characteristics of the sample will be reported as means and standard deviations for continuous variables, and frequencies and percentages for categorical variables. Analysis of variance and Chi-square tests will be conducted to determine differences in all variables between study group (i.e., control or intervention) at baseline.

Firstly, the appropriateness of the randomization process will be analysed by exploring outlier values and the normal distribution of the variables using the Kolgomorov–Smirnov test and graphical procedures (normal distribution plots). After inspecting outliers and extreme values, these will be winsorized using the 1st percentile and 99th percentile of the distribution of variables.

Secondly, analysis of covariance (ANCOVA) will be used to analyse the main effects of the study group (fixed factor) on cycling to school, ACS, PA levels, SDT-related variables in ACS, and individual, interpersonal, and environment variables related to ACS from the SEM (dependent variables). The effect size between groups will be calculated according to Lipsey and Wilson (2001), with the following formula: r = [t^2^/(t^2^ + gl)], where t = value of the Student t statistic and gl = degrees of freedom. Additionally, to examine change between baseline and post-intervention, regression models will be used, including the study group in the model as fixed factor and the mean difference (post-intervention minus baseline) of outcome variables as dependent variable.

Finally, to analyse the influence of covariates in the association of the intervention and the main outcome (i.e., cycling to school, ACS, and PA levels), mediation analyses will be performed using the PROCESS macro for SPSS (SPSS Inc., Chicago, IL, USA). For these analyses, the intervention will be included as independent variable and main outcomes as dependent (i.e., cycling to school, ACS and PA levels). Mediators that will be analysed are cycling knowledge, cycling skills, basic psychological needs satisfaction in ACS, motivation for ACS, barriers to ACS from adolescents and parents, and peer social support for ACS.

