**Environment**		
Distance home-school	Shortest route, real route	Google Maps Global Positioning System (GPS)
School Neighbourhood	Cycling lane length Bicycle racks	Geographical Information System Manual Search
Weather	Temperature (maximum, minimum, mean), total rainfall, and mean wind speed	National Weather Data Bank

**Table 2 ijerph-18-02066-t002:** Reach Effectiveness Adoption Implementation Maintenance (RE-AIM) components and dimensions to be evaluated in the PACO study.

RE-AIM Component	PACO Study
REACH (R)	The absolute number and proportion of participants recruited for the study given a target sample of 360 adolescents aged 14–15 years old from the 3rd grade of secondary education.
EFFECTIVENESS (E)	Main outcomes: cycling to school, ACS—walking and cycling, and PA Other variables: cycling knowledge, cycling skills, basic psychological needs satisfaction in ACS, motivation for ACS, barriers to ACS from adolescents and parents, and peer social support for ACS.
ADOPTION (A)	The absolute number and proportion of school staff who are willing to deliver the intervention. Alignment/consistency between intervention content and national educational policy [55].
IMPLEMENTATION (I)	Intervention fidelity: extent to which intervention agents deliver the intervention components as intended, including adaptations made, and of participant compliance with the intervention in terms of attendance. Cost of the intervention Process evaluation: participant feedback about enjoyment, usefulness, and potential improvements after each session. Participant focus groups and interviews with intervention agents at the end of the intervention to understand their experiences of the intervention.
MAINTENANCE (M)	Setting level: extent to which the intervention is delivered as part of the school PE curricula the following academic year. Individual level: follow-up questions to the PE teachers after 6 months post-intervention to assess the intervention´s maintenance.

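### The mediators are meant to show which intervention components work, but the course is tested as one package, attitudes to cycling have no cycling-specific pupil measure, and skills are not scored in controls

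*Protocol article*

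**What the plan says.** Section 1.3 gives the purpose of the mediation work: "several mediators have been identified in the PACO study to determine which components of an intervention contribute to behaviour change".

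Section 3.2 builds the course from three components (knowledge, skills and attitudes) and describes the attitudes component as "related to awareness, confidence, enjoyment, and usefulness of cycling". On delivery it says: "The 7 h intervention has four sessions that will be implemented during PE sessions over a period of one month". The comparator is stated in the Abstract: "the control group will continue their usual activities".

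Section 6 fixes the mediators: "Mediators that will be analysed are cycling knowledge, cycling skills, basic psychological needs satisfaction in ACS, motivation for ACS, barriers to ACS from adolescents". Its list ends with the barriers seen by parents and with support from peers. Section 4.1 places the assessments at baseline and "immediately after the intervention period for both intervention and control groups". In Table 2, the Implementation row adds, as process evaluation, "participant feedback about enjoyment, usefulness, and potential improvements after each session".

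**The concern.** A claim about which components contribute needs two things: a comparison in which the components vary separately, and a measure of what each component is supposed to change, taken in both arms. The article has the first for none of the three components. It has the second, in direct form, only for knowledge.

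What is at stake is how the mediation results are read. Section 7 says mediators must be measured because behaviour is hard to change through schools. If cycling to school does not change, the trial could not tell whether pupils' confidence in cycling, or their enjoyment of it, failed to move or moved without changing behaviour. If behaviour does change, the effect may be credited to whichever construct happened to be measured.

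**Working it through.** No figure in the plan underlies this point, so the check sets the passages side by side and counts.

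**Step 1: contrasts against components.** Let K, S and A indicate that a school is offered the knowledge, skills and attitudes components.

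- Intervention schools: (K, S, A) = (1, 1, 1).
- Control schools: (K, S, A) = (0, 0, 0).

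The three columns are identical, so their rank is 1. Three separate component effects would need rank 3. The only variation in receipt built into the plan is in section 4.2.2, where entry to the on-road session depends on the score in the traffic-free session. That variation follows from pupil performance and is not randomised, so it does not separate the components either.

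**Step 2: each component mapped to a measure.**

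| Component | Measure | Baseline and follow-up | Control arm |
|---|---|---|---|
| Knowledge | 20-question test (4.2.2) | Under the general schedule in 4.1; its own timing is not stated | Could be taken |
| Skills | Observer checklists in sessions 2 and 3 (4.2.2) | No; conceded in section 7 | No |
| Attitudes to cycling | No cycling-specific pupil scale in 4.2.1, 4.2.2 or Table 1 | General proxies only | General proxies only |

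So 1 of 3 components has a direct measure that both arms could take.

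**Step 3: how close the proxies come.** Three pupil scales in section 4.2.2 fall under the before-and-after schedule in both arms.

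- Need satisfaction includes competence, but its lead question asks about the pupil's usual mode of travel. Section 1.1 cites Spanish rates of cycling to school of 0.3% and of less than 2%. If those rates apply to this sample (an assumption), 0.003 × 360 = 1.1 and 0.02 × 360 = 7.2. About 1 to 7 of 360 pupils would then be answering about cycling at baseline.
- Motivation uses a stem that pools walking with cycling. Section 1.1 says about 50% of adolescents already walk. On the same assumption that is 0.5 × 360 = 180 pupils, whose answers may reflect walking.
- Adolescent barriers concern active commuting in general.

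The only separate cycling scale is in the parental barriers questionnaire, and it does not measure pupils' attitudes. Section 1.1 itself criticises earlier reviews for pooling the two modes and says that their correlates differ.

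**Step 4: skills as a mediator.** An indirect effect is a × b, where a is the effect of group on the mediator and b is the effect of the mediator on the outcome given group. Estimating a needs mediator values in both arms. Controls have no skills score, so any model restricted to pupils with a score contains intervention pupils only. Group is then constant and a cannot be estimated.

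**The case against.** The strongest case on the other side has four parts.

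1. The sentence in section 1.3 is introductory. Section 6 analyses named mediators, section 7 speaks of identifying pathways, and no planned analysis estimates a component effect. This stands, and it makes the rewording easy. It does not make the sentence correct, because it states an aim that the design cannot meet.

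2. The mediators come from self-determination theory and the social-ecological model and need not match the curriculum labels one to one. This is fair. It is why a new attitude block should be exploratory, and why stating the limit openly is an acceptable alternative.

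3. The items of the Student questionnaire are not reproduced, and a fuller assessment description is published elsewhere, so some items may touch cycling confidence or usefulness. That is possible. However, Table 1, the mediator list in section 6 and the Effectiveness row of Table 2 all leave attitudes to cycling out.

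4. The limitations in section 7 already concede the missing skills assessment. They do, but section 6 still lists skills as a mediator.

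A reader might go further and infer that the attitudes component has no usable data at any time in either arm. The documents do not support that: the general scales are scheduled before and after in both arms, and session feedback exists in the intervention arm. A reader might also infer from section 1.1 that attitudes are where the course is most likely to act. That passage reports gains in confidence, knowledge, skills and attitudes together and does not rank them.

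**Conclusion.** The point holds as a limit on what the mediation analysis can claim. There is one randomised contrast for three components, so no component effect is identified. One of the three components (knowledge) has a direct test open to both arms. One (skills) is observed only in the intervention arm. One (attitudes to cycling) is covered only by general active-commuting proxies and by one-arm feedback.

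It would be too strong to say that the mediation question cannot be answered at all. Pathways through knowledge, motivation, need satisfaction and barriers can still be described. The primary outcomes and the comparison between groups do not change.

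The conclusion assumes that the knowledge test follows the general before-and-after schedule in both arms, and that the Student questionnaire contains no unlisted cycling-attitude scale. The counts of 1 to 7 and 180 pupils further assume that the national rates in section 1.1 apply to this sample. They illustrate the weakness of the proxies, and the conclusion does not depend on them.

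**What to change.** 1. In section 1.3, replace the aim about components with: which measured pathways are consistent with the effect of the whole course. This brings it into line with section 7. Add that the components cannot be separated by design.
2. Add a short block on cycling to school (confidence, enjoyment, usefulness) to the Student questionnaire at baseline and follow-up in both arms, and list it in section 6 as an exploratory mediator. If the questionnaire can no longer be changed, state that attitudes are covered only by scales on active commuting in general.
3. In section 6, remove observed cycling skills from the mediators of the between-group effect, because controls are not scored. The checklists can still be reported descriptively within the intervention arm.

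Items 1 and 3 are changes of text. Item 2 costs a few minutes of pupil time in a questionnaire already given twice to both arms, and one more secondary variable to report.
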